## Abstract

**Background:**

Post-term pregnancy, a pregnancy exceeding 294 days or 42 completed weeks, is associated with increased perinatal morbidity and mortality and is considered a high-risk condition which requires specialist surveillance and induction of labour. However, there is uncertainty on the policy concerning the timing of induction for post-term pregnancy or impending post-term pregnancy, leading to practice variation between caregivers. Previous studies on induction at or beyond 41 weeks versus expectant management showed different results on perinatal outcome though conclusions in meta-analyses show a preference for induction at 41 weeks. However, interpretation of the results is hampered by the limited sample size of most trials and the heterogeneity in design. Most control groups had a policy of awaiting spontaneous onset of labour that went far beyond 42 weeks, which does not reflect usual care in The Netherlands where induction of labour at 42 weeks is the regular policy. Thus leaving the question unanswered if induction at 41 weeks results in better perinatal outcomes than expectant management until 42 weeks.

**Methods/design:**

In this study we compare a policy of labour induction at 41 + 0/+1 weeks with a policy of expectant management until 42 weeks in obstetrical low risk women without contra-indications for expectant management until 42 weeks and a singleton pregnancy in cephalic position. We will perform a multicenter randomised controlled clinical trial. Our primary outcome will be a composite outcome of perinatal mortality and neonatal morbidity. Secondary outcomes will be maternal outcomes as mode of delivery (operative vaginal delivery and Caesarean section), need for analgesia and postpartum haemorrhage (≥1000 ml). Maternal preferences, satisfaction, wellbeing, pain and anxiety will be assessed alongside the trial.

**Discussion:**

This study will provide evidence for the management of pregnant women reaching a gestational age of 41 weeks.

**Trial registration:**

Dutch Trial Register (Nederlands Trial Register): NTR3431. Registered: 14 May 2012.

## Background

Post-term or prolonged pregnancy, defined as a pregnancy extended to or beyond 42 + 0 weeks or ≥ 294 days after the first day of last menstrual period, is associated with increased perinatal morbidity and mortality [1–10]. Therefore post-term pregnancy is considered as a high-risk condition which requires specialist surveillance and induction of labour at some stage, mainly because of a relative small group of undetected growth-restricted foetuses that is at risk for adverse perinatal outcome [11, 12].

In this era, with gestational age based on first trimester ultrasound, the incidence of post-term pregnancy is reduced to 3-5% or even less [13–15]. The risk on adverse perinatal outcome is considered to increase gradually rather than a steep increase from 42 weeks onwards, though the literature on this subject is ambiguous [16–18]. The Cochrane review on induction of labour for improving birth outcomes showed that a policy of labour induction at or beyond 41 completed weeks is associated with significant fewer perinatal deaths (22 trials, 9383 participants, RR 0.31 [95% CI 0.12-0.88]) although the absolute risk of perinatal death is small [18]. According to this review, labour induction doesn’t increase the risk of Caesarean section in women with a gestational age of 41 or 42 completed weeks [18]. However, only a few of the included studies had a policy of labour induction at 41 weeks in the intervention group. In other studies it is unclear whether labour was always induced at 41 weeks. Furthermore in most trials expectant management in the control groups continued far beyond 42 weeks [17–20]. In addition, recent observational studies showed that elective induction leads to similar increased maternal and foetal risks as induction on medical indication, in comparison to spontaneous onset of labour [21]. Recent meta-analysis showed that induction of labour on maternal or foetal indication in women with intact membranes reduces the risk of Caesarean section, thus leaving the question unanswered if induction at 41 weeks in obstetrical low risk women gives better perinatal outcomes and maternal outcomes than expectant management until 42 weeks [19, 22].

Because of the uncertainty regarding the management of (impending) post-term pregnancy, there is no consensus on the optimal timing of induction, leading to practice variation. Policy concerning low risk pregnancies at or beyond 41 weeks in the Netherlands varies from expectant management until 42 weeks, without extra surveillance, to once or twice a week cardiotocography (CTG) and ultrasound surveillance in secondary care from 41 weeks onwards and labour induction at 42 weeks, or labour induction starting at 41 weeks [23]. Until now, the interdisciplinary agreement between the Royal Dutch Organisation of Midwives (KNOV) and the Dutch Society for Obstetrics and Gynaecology (NVOG) concerning post-term pregnancy in the Netherlands, indicates secondary care and labour induction from 42 weeks onwards [8, 24]. However, more and more hospitals are converting their policy to induction of labour at 41 weeks, though there is no consensus concerning this change of policy. Opponents argue that hospitalised labour will diminish physiological birth, with increased rates of pain treatment, and operative delivery (vacuum/forceps c.q. Caesarean section) resulting in more negative birth experiences and an increase in costs with doubtful perinatal benefits [20, 25–28]. Unfortunately, data reflecting the Dutch situation, comparing induction of labour at 41 weeks with expectant management until 42 weeks, are lacking.

Observational data of the Dutch Perinatal Registry (PRN 2000 - 2006) show very small, but increasing rates of adverse perinatal outcomes such as Apgar score <7 (40 + 0-40 + 6 weeks 0.9%, 41 + 0-41 + 6 weeks 1.1% and ≥ 42 weeks 1.4%), meconium aspiration syndrome (40 + 0-40 + 6 weeks 0.12%, 41 + 0-41 + 6 weeks 0.21% and ≥ 42 weeks 0.25%) and NICU admission (40 + 0-40 + 6 weeks 0.49%, 41 + 0-41 + 6 weeks 0.62% and ≥ 42 weeks 0.91%), among births from singleton pregnancies [29].

However, perinatal mortality (up to 28 days) of singletons born between 41 + 0 – 41 + 6 weeks (0.16%) was comparable to perinatal mortality between 40 + 0 – 40 + 6 weeks (0.13%) and between 39 + 0 – 39 + 6 weeks (0.16%) [30]. PRN data also showed an increase in operative vaginal delivery when labour is induced beyond 41 weeks compared to induction at term (37 + 0-39 + 6 9.8%, 40 + 0-40 + 6 weeks 12.4%, 41 + 0-41 + 6 weeks 14.6% and ≥ 42 weeks 17.1%) [31].

Previous studies comparing expectant management and induction of labour in high risk pregnancies showed a discrepancy between observational PRN data and data from randomised trials (Digitat trial (growth retardation) and Hypitat trial (hypertension at term)) [32, 33]. The PRN database indicated an increased risk of operative vaginal delivery after induction of labour, whereas the subsequent randomised clinical trials showed that such an effect was absent [32–34]. Also PRN data showed a significant increase in Caesarean section after labour induction at or beyond 41 completed weeks compared to spontaneous onset of labour. However, Caesarean section rates in the Netherlands between 2000-2006 are much lower than in many other western countries (for singletons overall 9.4% between 41 + 0-41 + 6 weeks and 16.6% beyond 42 weeks) thus hampering the extrapolation of results from international studies, and emphasising the importance of this trial [29, 30].

Ethnic differences are likely to play an important role in post-term pregnancy. The mean duration of pregnancy is shorter in women from African origin and Indian origin as compared to Caucasian women [35]. Indeed, the incidence of stillbirth is higher from 41 weeks onwards among women from African and Surinam-Hindustan (Indian) origin as compared to Caucasian women [35, 36]. Though guidelines are not adjusted yet to ethnic origin, we will register ethnicity in our study.

We are not aware of other ongoing studies that are similar to the present study proposal or related to the problem discussed here (national or international). The issue of the timing of induction of labour in post-term pregnancy has been addressed in many studies showing that labour induction should be offered in case of post-term pregnancy because of the increased risk of perinatal mortality and morbidity [8, 19].

The 41-42 weeks dilemma considers a large proportion of pregnant women, as with a policy of labour induction at 41 weeks 18% (31,166/173,099) of all pregnant women in The Netherlands would be induced, compared to 1.5% (2,525/173,099) at 42 weeks [37]. With a policy of expectant management 68.7% will have spontaneous onset of labour between 41 + 0 – 41 + 6 weeks [37]. Before the introduction of the most recent guideline on management of post-term pregnancy in 2007 [38], there were less inductions of labour between 41 + 0 and 41 + 6 weeks (2006 18,2% (30,903), 2007 18,0% (30,151) and more deliveries after 42 weeks (2006 4,9% (8,312), 2007 4,5% (7,550)) [39].

Because of the controversy on this issue between caregivers, and the fact that the policy in surrounding countries is different, we feel that a nationwide randomised clinical trial is the obvious and necessary step to come to a multidisciplinary guideline regarding (impending) post-term pregnancy. We will conduct a randomised controlled trial to evaluate the effectiveness of a policy of labour induction at 41 weeks compared to expectant management until 42 weeks in women without contra-indications for expectant management.

## Methods/design

The study is set in the Dutch Obstetric Consortium: a collaboration of obstetric centers in the Netherlands in cooperation with the Midwifery Research Network of the Netherlands (MRNN) [40]. Approximately 200 centers, including university hospitals, teaching hospitals, non-teaching hospitals and midwifery practices will participate in this trial [24].

We will ask obstetrical low risk women ≥ 18 years with a singleton pregnancy in stable cephalic position and a certain gestational age of 40 + 5 - 41 + 0, based on first trimester ultrasound and without contra-indications for expectant management until 42 weeks for consent to participate in our study and to be allocated to induction of labour at 41 + 0/+1 weeks or at 42 + 0 weeks. Exclusion criteria are age <18 years, uncertain gestational age, obstetrical indications for secondary care (e.g. hypertension (systolic 140 mmHg and/or diastolic 90 mmHg or more), proteinuria (≥3 g/L), pre-existent maternal heart or kidney diseases, gestational diabetes, previous Caesarean section, multiple pregnancy, intra-uterine growth retardation) and non-reassuring fetal status (no fetal movements, abnormal fetal heart rate, known fetal abnormalities which could influence perinatal outcome, including abnormal karyotype, ruptured membranes at time of randomisation and a non-reassuring fetal status at time of randomisation). The results of the randomised clinical trial will be analysed according to the intention to treat principle.

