### Intervention group: induction of labour at 41 + 0 or 41 + 1 weeks

Women randomised to induction of labour will be referred to the cooperating hospital for induction of labour according to local protocol. Induction of labour will be started at 41 + 0 to 41 + 1 weeks. Women with a cervix that is judged to be ‘ripe’ at vaginal examination (Bishop Score of 6 or more), will have labour induced with amniotomy followed by intravenous oxytocin according to local protocol. In case rupturing of membranes is not possible, cervical ripening will be accomplished in accordance with our national guidelines. In case the cervix is judged to be still unripe the day after priming, cervical ripening will be repeated. All patients in the intervention group will be monitored until after delivery.

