### Control group: expectant management until 42 weeks

Women allocated to expectant management await spontaneous onset of labour until 42 weeks. If labour has not started, monitoring is according to local protocol. This reflects current care in The Netherlands. Monitoring can consist of consultations, electronic fetal heart rate monitoring and ultrasound assessment of amniotic fluid. An increase of the frequency of these checks as well as admission to the hospital is based on the judgment of the midwife or clinician in charge as usual. In the expectant management group, intervention will occur in case the fetal condition does not justify expectant management, such as reduced fetal movements reported by the mother, non-optimal fetal heart rate on CTG or oligohydramnios [12]. If an indication for induction of labour occurs, such as prelabour rupture of membranes for >24 hours or meconium stained amniotic fluid, referral to secondary care for labour induction is indicated according to the management strategies which are recorded in the national Obstetrical Indication List [41]. All diagnostic tests and interventions between randomisation and birth are registered in the case report form. Protocol violation is noted in the case report form with the reason of switch of policy to induction of labour. Women with uncomplicated pregnancies who are still in primary care will be referred to secondary care at 42 + 0 weeks for induction of labour following the procedure as stated for the intervention group.

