### Measurements

When a patient fulfils the study criteria and written informed consent is obtained, clinical data such as age, height, weight before pregnancy, ethnicity, highest finished education and social economic status based on postal code are collected at study-entry [44]. Obstetric history and level of care in current pregnancy are registered. Cervical ripeness will be assessed by digital examination of the cervix. The acquired Bishop score (based on dilatation, effacement, consistency, position and engagement) will be noted and fetal condition will be checked according to local protocol. Eligible women will be randomised subsequently.

After randomisation, number and lengths of admissions is noted. In the expectant management group, level of care and number of (outpatient clinic) visits is reported. At each visit, maternal and fetal assessments are recorded.

At the onset of labour all relevant data will be collected including start of labour. Data on first, second and third stage of labour are collected, including treatment for pain relief, mode of delivery and adverse perinatal and maternal outcomes.

Perinatal and maternal mortality and morbidity will be specified.

Data will be collected until women and child are discharged home for the first time or when deceased. If a participant withdraws from the study, the reason (lost to follow up, withdrawal of consent, prematurely stop of study) will be registered.

We will use standardised case report forms that have been established in previous studies.

Apart from the collection of clinical data, a sub-cohort of women will complete questionnaires addressing health related quality of life and wellbeing (EQ 6D [45], state anxiety (STAI [46]), preferences and satisfaction (SSQ [47, 48], LADY-X [49]), as well as questionnaires containing information on pain (PCS [50], NPRS/VAS) [51, 52]. Questionnaires will be completed at baseline after randomisation, and 6 weeks after delivery. Women can fill out the questionnaires online or on paper.

Women who do not give consent for randomisation will be treated according to the local protocol and they will be followed in a prospective cohort study.

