#### Data analysis

The results of the randomised clinical trial will be analysed according to the intention to treat principle. The effectiveness of labour induction at 41 weeks versus expectant management until 42 weeks will be assessed by calculating relative risks and 95% confidence intervals. Time to delivery will be compared using Kaplan-Meier curves and log-rank tests.

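### Allocation is possible from 40+5 but the policies part only at 41+0/+1, so the intention-to-treat difference understates any difference among women who reach 41 weeks

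*Protocol article*

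**What the plan says.** Methods/design seeks consent and allocation from women at "a certain gestational age of 40 + 5 - 41 + 0, based on first trimester ultrasound and without contra-indications for expectant management until 42 weeks". Under Measurements, after consent, cervical assessment and a check of fetal condition, "Eligible women will be randomised subsequently". The article states no rule that delays allocation to 41+0.

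In the intervention arm, "Induction of labour will be started at 41 + 0 to 41 + 1 weeks". In the control arm, "Women allocated to expectant management await spontaneous onset of labour until 42 weeks". So the planned care is the same in both arms until 41+0 at the earliest.

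The Discussion paragraph of the Abstract says that the trial will inform the "management of pregnant women reaching a gestational age of 41 weeks". Under Data analysis, "The results of the randomised clinical trial will be analysed according to the intention to treat principle"; no other analysis set is named. The sample size section uses a non-inferiority test with a 0.020 absolute margin at one-sided 0.05, a rate of 3% in the standard group and 900 women per group. It adds a fallback power of 85% for 3% versus 1%. Neither figure mentions women who labour before the policies part.

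**The concern.** A woman allocated at 40+5 who goes into labour at 40+6 has followed her allocation but never faced the choice between induction at 41 weeks and waiting until 42. She stays in the denominator of her arm, with the same expected outcome whichever arm that is. The more such women there are, the smaller the observed difference becomes relative to the difference among women who do reach 41+0.

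In a superiority trial this only costs power. Here the primary test has a fixed absolute margin, so shrinkage towards zero makes a finding of non-inferiority easier. The Discussion says that a low and comparable incidence would itself be an argument against intervention. A diluted difference could therefore be read as reassurance about women reaching 41 weeks that the data support less well than they appear to.

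**Working it through.** **Inputs from the protocol article.** 900 per group, margin 0.020, one-sided 0.05, standard-group rate 0.030, expected difference 0, fallback 3% versus 1% (Sample size calculation); allocation window 40+5 to 41+0 (Methods/design); 68.7% spontaneous onset over 41+0 to 41+6 (Background).

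**Not in the article, so assumed.** The onset rate before 41+0, and the spread of randomisation days over the window.

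**1. The plan's own figures.**
- Non-inferiority: n = (1.645 + 0.842)² × 2 × 0.03 × 0.97 / 0.02² = 900 per group. This matches.
- Superiority, 3% versus 1%, 900 per group, two-sided 0.05, normal approximation: 85.8%. This agrees with the stated 85%.

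**2. Share f in labour before the policies part.** The only onset rate given is "With a policy of expectant management 68.7% will have spontaneous onset of labour between 41 + 0 – 41 + 6 weeks". At a constant rate that is 1 − (1 − 0.687)^(1/7) = 15.3% per day. It applies after 41+0 and is probably too high before it, so I use 8-15% per day. Cumulative onset is 1 − (1 − d)^k for daily rate d over k days:

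| Randomised at | Before 41+0, d = 8% | Before 41+0, d = 15% | Before 41+1, d = 8% | Before 41+1, d = 15% |
|---|---|---|---|---|
| 40+5 | 15% | 28% | 22% | 39% |
| 40+6 | 8% | 15% | 15% | 28% |
| 41+0 | 0% | 0% | 8% | 15% |
| Mean, even spread | 8% | 14% | 15% | 27% |

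With d = 15.3% the two upper means are 14.5% and 27.6%. So f is about 8-15% to 41+0, and up to about 28% to 41+1.

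**3. Dilution.** If gap women have the same risk in both arms, the intention-to-treat difference is (1 − f) × the difference among women still undelivered. A true 2.0 points becomes 0.92 × 2.0 = 1.84 at f = 8% and 0.85 × 2.0 = 1.70 at f = 15%.

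**4. Consequences with 900 per group.** The chance of declaring non-inferiority is Φ((0.02 − diff)/SE − 1.645), with unpooled SE. Gap women are given a 3% risk in both arms. Among women reaching 41+0, either induction is worse (5% versus 3%) or expectant management is worse (3% versus 1%). Superiority power is for the second case.

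| f | Declared non-inferior, induction worse | Declared non-inferior, expectant worse | Superiority power |
|---|---|---|---|
| 0 | 5.0% | 5.0% | 85.8% |
| 8% | 7.1% | 8.0% | 78.1% |
| 15% | 9.4% | 11.4% | 70.1% |

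Worked line, f = 15%, induction worse: arm rates 4.7% and 3.0%, SE = 0.00906, Φ(0.003/0.00906 − 1.645) = 9.4%.

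**5. Sensitivity.** In the expectant-worse case, if gap women have a 1% risk instead of 3%, the chance of declaring non-inferiority is 8-12% and power is 81-76% over the same range of f.

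**The case against.** The strongest reply is that nothing is mis-stated. The objective at the end of the Background compares two policies in women without contra-indications to waiting, and does not restrict itself to women undelivered at 41+0. Intention to treat validly estimates the effect of assigning a policy from 40+5. The margin and the 3% are set for the randomised groups, and under that null the error stays at 5%. This stands. A reader might infer that the sample size is wrong or that the test's error rate is inflated as defined. The article supports neither: the excess over 5% appears only when the 2-point difference is placed in women who reach 41+0.

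A reader might also infer an overall dilution of 15-25% before 41+0, with power falling to 57%. At 8-15% per day that would need most women to be randomised early in the window, and the article gives no such distribution. Shares of that order arise under an even spread only if the gap is counted to 41+1.

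The exact day of allocation and any supplementary analysis may be set out in the full protocol or analysis plan. Part of the re-check exists already, because ruptured membranes and non-reassuring fetal status at randomisation are exclusions. With about 200 centres and referral to hospital for induction, some lead time is a defensible trade-off.

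What remains is that the window is stated here, the Abstract frames the evidence as being about women reaching 41 weeks, and the only named analysis is diluted for that group in the direction that favours a claim of equivalence.

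**Conclusion.** The point holds as a gap between the population analysed and the population to which the conclusion is addressed. It is not an error in the sample size or in the use of intention to treat. The direction follows from the text; the size does not. It rests on 8-15% onset per day before 41+0, an even spread of randomisation over the window, equal risk in both arms for women who labour in the gap, and a normal approximation. On those terms the effect is moderate: a 7-11% chance, rather than 5%, of declaring non-inferiority when the true difference in women reaching 41+0 equals the margin, and a loss of about 8 to 16 points of superiority power in those women. If most women are randomised at 41+0 it is smaller; if many are randomised at 40+5, or induced at 41+1, it is larger.

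**What to change.** Keep intention to treat in all randomised women as the primary analysis. Pre-specify a supplementary analysis of the primary outcome, as allocated, in all women of both arms who are undelivered and not in labour at 41+0. Report it beside the main result, and let it qualify any claim of equivalence for women reaching 41 weeks.

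Report by arm the share delivered or in labour before 41+0. The trial is open label and intervention women are referred to hospital, so balance in this subset is likely but not guaranteed. A selection based on whether women were actually induced would not serve, because it would remove women from one arm only.

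Where booking allows, perform the web-based allocation as close to 41+0 as feasible, with consent and baseline data still taken from 40+5.

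Cost: the analysis needs only the start of labour, which Measurements already lists. It is less precise. With 900 × 0.92 = 828 or 900 × 0.85 = 765 women per arm and 3% in both, non-inferiority power is Φ(0.02/√(2 × 0.03 × 0.97/n) − 1.645), about 77% or 74% instead of 80%. That is one reason to use it as a qualifier rather than as a second mandatory test. Later allocation shortens the notice for arranging induction, and some consenting women will labour before they can be randomised.
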